### 8.2.4 STATISTICAL METHODS FOR THE PRIMARY OBJECTIVES

Analysis of Covariance (ANACOVA) will be used to compare the main outcome measures in the intervention groups at week 26 and week 52 using the data from CID2 (after weight-loss, adults) or CID1 (children) as covariate.

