Primary outcome measures for adults are body weight loss maintained (kg), change in body composition, proportion of subjects maintaining > 0, 5 and 10% weight loss, and drop-out rate. Other non-clinical primary measures are to identify biological and psychological traits that determine the family's and individual's responses to the dietary interventions. Secondary end-points are reduction in abdominal obesity, changes in risk factors of type-2 diabetes and CVD and appetite/satiety hormones, and changes in physical activity. Clinical measurements will include in addition the identification and quantification of adipose tissue mRNA and peptide biomarkers. Primary outcome measures for children are changes in the proportion of overweight and obese children at 6 mo, and changes in BMI, and % whole body fat. Secondary end-points for overweight children are reduction in abdominal obesity, changes in waist-hip circumference ratio and blood parameters and changes in physical activity. A sub-study (described below) will assess the effect and safety of the high protein diet in children and adolescents. Dietary effects on bone and kidney health will be assessed and primary safety end-points will include changes in urinary and blood proteins, such as albumin and creatinine.

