### Dietary periods

- 1) Adult subjects only: 8 week Low Calorie Diet (LCD) period (liquid formula diet, 800-1000 kcal/day).
- 2) 6 months dietary intervention period 1 (SUPERMARKET period) followed by
- 3) 6 months dietary intervention period 2 (DIETARY INSTRUCTION period).
- 4) 12 months free-living period with no dietary intervention.

[figure not shown]

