### **Dietary intervention study**

All adult subjects will for the first 8 weeks of the study be submitted to an 800-1000 kcal/day LCD diet combined with instructions on behaviour modification. Only families where at least 1 parent has achieved a >8% weight loss will be included in the intervention study. The study consists of a 6-month dietary intervention period (period 1, SUPERMARKET period) where families obtain free food from an on-site supermarket and receive continual dietetic guidance, followed by a further 6-month period (period 2, DIETARY INSTRUCTION period) where families receive dietary and behavioural instruction. Families will regularly visit RVAU/UM throughout the intervention period for weighing and dietary instruction. There are 4 Clinical Investigation Days (CIDs) planned during the study, when anthropometric and other measures will be taken. CID 1 will take place in the 3 weeks prior to the LCD diet. CID 2, 3 and 4 will take place in weeks 0, 26 and 52, respectively.

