#### **7.1.2.2 Visit 2, CID 1 (between week -12 and -9)**

This baseline examination will register the following parameters:

- Anthropometric measures including:
  - Weight (all children)
  - Height (all children)
  - Waist/hip (overweight children only)
  - Body composition (DEXA/bioimpedance) (overweight children aged >12 years only)
- Physical activity scheme

- 3-day diet record (overweight children only)
- Fasting blood samples (all children)
- BP (overweight children only)

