#### **7.1.2.3 Visit 3, randomisation family meeting (week 0)**

*NB: Children participation preferred but optional*

Registrations include (all children):

- Weight
- Height
- Dietary instruction
- Adverse events & concomitant medication

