### 8.2.5 PRIMARY HYPOTHESIS

The following primary hypothesis can be applied:

H0: The 1o outcome (weight, etc) is equal in the intervention groups at week 26 and week 52, when controlling for the value in CID2 (adults) or CID1 (children).

vs.

H1: The 1o outcome is different in the intervention groups at week 26 and week 52, when controlling for the value in CID2 (adults) or CID1 (children).

The changes in continuously distributed variables from baseline to week 26 and week 52 within treatment groups will be tested with the paired t-test or the Wilcoxon-Signed-rank test, depending on distribution (all tests two-sided).

All categorical variables will be expressed in contingency tables and analyzed using Fisher's exact test. Survival analysis using the Kaplan-Meier plot and the log-rank test will be used to investigate time to subject withdrawal.

All null hypotheses comparing groups assume equality between the treatment groups while the alternative hypotheses assume that there is a difference (two-sided). All within-group null hypotheses assume no change from baseline to week 26 or week 52 while the alternative hypotheses assume that there is a change (two-sided).

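### Children's change outcomes start at CID 1, 9–12 weeks before randomisation, so the 6-month figures cover 35–38 weeks and cannot be read as change on the diet

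*Protocol*

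**What the plan says.** All references are to the protocol.

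- **Covariate.** Section 8.2.4 compares the main outcomes at weeks 26 and 52 by ANCOVA "using the data from CID2 (after weight-loss, adults) or CID1 (children) as covariate". Sections 8.2.5 and 8.2.6 use CID 1 for children in the same way.
- **Timing of CID 1.** The children's visit list has "Visit 2, CID 1 (between week -12 and -9" and introduces it with "This baseline examination will register the following parameters". The synopsis adds "CID 1 will take place in the 3 weeks prior to the LCD diet". The LCD itself is described as "Adult subjects only: 8 week Low Calorie Diet (LCD) period".
- **Later visits.** Randomisation is at week 0, children's CID 2 at week 4, CID 3 at week 26 and CID 4 at week 52.
- **Week 0.** Section 7.1.2.3 lists weight and height for all children, with the note "Children participation preferred but optional". Body composition and blood samples are not taken then.
- **Outcomes.** The synopsis names "changes in the proportion of overweight and obese children at 6 mo, and changes in BMI" and percentage body fat. Section 8.2.2 adds a 12-month time point and specifies age-associated BMI.
- **Within-group tests.** Section 8.2.5 plans paired tests of change, and states "All within-group null hypotheses assume no change from baseline to week 26 or week 52".

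**The concern.** Adults are analysed from CID 2, the value at the end of the LCD and the start of the diets. Children are analysed from a value taken before the LCD began, and the protocol gives no reason for the difference. Section 8.2.5 does not say in so many words which visit is the baseline for the children's within-group tests. CID 1 is the natural reading, because the visit list calls it the baseline examination and the same section controls for it.

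On that reading, a paired test to week 26 credits the assigned diet with whatever happened in the 9–12 weeks before it started. A child who crosses the overweight threshold in that window counts as a change at 6 months. The window is also not an ordinary one: the parents are on the LCD and receive dietary and behavioural instruction, and a family is randomised only if at least one parent loses more than 8% during it. A reader of the results would take a 6-month change to mean 6 months on the diet.

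**Working it through.** The protocol gives no sample size, power or precision figure for the children's outcomes, so there is none to reproduce. The check is arithmetic on the visit schedule, plus a precision calculation under stated assumptions.

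**Inputs.** CID 1 lies p = 9 to 12 weeks before week 0 (Section 7.1.2.2). Assessments are at T = 26 and 52 weeks (Sections 7.1.2.9 and 7.1.2.11).

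**Share of the interval before randomisation, p/(p + T):**

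- Week 26: 9/35 = 25.7% to 12/38 = 31.6%, with an interval of 35–38 weeks.
- Week 52: 9/61 = 14.8% to 12/64 = 18.8%, with an interval of 61–64 weeks.

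The synopsis places CID 1 in the 3 weeks before an 8-week LCD. Taken literally, that is week -11 to -8 and gives 8/34 = 23.5% to 11/37 = 29.7% at week 26. The conclusion does not change.

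**Effect on within-group change (assumed drift).** If BMI drifts by 0.01–0.02 units per week with no diet effect, the change from week -12 to week 26 is 38 × 0.01 = 0.38 to 38 × 0.02 = 0.76. From week 0 it is 26 × 0.01 = 0.26 to 26 × 0.02 = 0.52. The excess is 0.12–0.24 units. The drift is an assumption, not a protocol figure.

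**Effect on the between-arm comparison.** A simulation used 3,000 runs, two arms of 50 children, no diet effect, the drifts above or none, a between-child SD of 3 BMI units, and random-walk noise with SD 0.12 per square-root week, all assumed. ANCOVA on the week -12 value gave mean differences within 0.006 units of zero and type I error of 4.3–5.4%. With a week-0 covariate, type I error was 4.9–5.7%. The standard error with the week -12 covariate was about 1.2 times that with week 0.

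**How far the precision loss depends on assumptions.** Let the variance of true change be σ² per week and measurement error variance be e² at each visit. The variance ratio for change is then approximately ((p + 26)σ² + 2e²)/(26σ² + 2e²).

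- With e² = 0: 35/26 = 1.35 to 38/26 = 1.46, a standard-error ratio of 1.16–1.21.
- With 2e² = 26σ², so that error contributes as much as 26 weeks of true change: 61/52 = 1.17 to 64/52 = 1.23, a ratio of 1.08–1.11.

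The ratio tends to 1 as measurement error dominates.

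**The case against.** The strongest reply is that the main comparison is between arms and CID 1 is a legitimate pre-randomisation covariate. This stands. A reader might infer that the early baseline biases the diet comparisons; it does not, because the lead-in is common to all arms.

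A second reply is that the week-0 value, as scheduled, is not a better baseline. This also stands.

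- Section 7.2.1 requires underwear, fasting and an empty bladder only at CIDs; elsewhere only coat and shoes come off. Children's Visit 3 is not a CID. If clothing adds 0.5–1 kg in a child of 1.45 m (assumption), BMI rises by 0.5/1.45² = 0.24 to 1/1.45² = 0.48 units. That is at least as large as the 0.12–0.24 units to be removed, and it would look like weight loss in every arm.
- Sections 7.1.1.6 and 7.1.1.7 put a week-0 family meeting, with a similar note on children's attendance, after randomisation. If children are measured then, attendance could depend on the allocated arm.

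These points set conditions on the fix; they do not remove the labelling problem.

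Three further replies limit the argument. Age-associated BMI in Section 8.2.2 takes account of much ordinary growth. Children are not energy restricted during the LCD (Section 3), so a household effect is possible, but no figure in the protocol supports one. Regression to the mean is a weak argument, because CID 1 is already a separate measurement from screening. Finally, CID 2 in week 4 follows randomisation and is rightly not used as covariate.

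**Conclusion.** The point holds for within-group change in children and for the change in the proportion overweight or obese. With CID 1 as baseline, the week-26 figures cover 35–38 weeks, 26–32% of it before any study diet, and the week-52 figures carry 15–19%. These shares need only the visit schedule and the reading of CID 1 as baseline.

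For the between-arm ANCOVA the cost is precision alone, and its size is not fixed by the documents. The standard-error ratio of about 1.2 requires variance of change proportional to time and negligible measurement error. A reader might turn the shares into a loss of 26–32% of the children's information; that rests on the same assumption and should not be stated as a finding. Nor do the documents support saying that the parents' LCD did alter the children's weight, only that the interval cannot exclude it.

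This should be corrected, but it does not threaten the randomised comparisons.

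**What to change.** 1. In Section 7.1.2.3, make the child's attendance at week 0 required for weight and height. State that they are taken before the family learns its allocation and under the CID weighing conditions of Section 7.2.1.
2. In Sections 8.2.4 and 8.2.5, name this week-0 value as the baseline for within-group change in age-associated BMI and in overweight/obese status, and as the ANCOVA covariate for BMI. Use CID 1 where week 0 is missing, and add a sensitivity analysis with CID 1 for all children.
3. Keep CID 1 for percentage body fat and blood markers, which have no week-0 value. Report those changes to week 26 as running from CID 1 over 35–38 weeks, including the LCD period, with no within-group claim of a 26-week diet effect.

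The cost is modest but more than a change of covariate. Children must attend an existing visit that is now optional, under stricter weighing conditions and with measurement ordered before disclosure. Some week-0 values will still be missing, so the BMI baseline will mix two time points; the sensitivity analysis shows whether that matters.

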## Aims

The main objective of the DiOGenes study is to identify the efficacy of particular diets for protection against weight gain and weight regain, in a susceptible population of obese and overweight individuals and their children. The overall study comprises a 6 to 12 months dietary intervention study in 350 families in 8 European countries (Denmark, the Netherlands, UK, Germany, Spain, Greece, Bulgaria and the Czech Republic), investigating the effect of different dietary components (high/normal protein and high/low GI) on maintenance of weight loss and prevention of weight (re)gain. In Denmark/Netherlands the study will be carried out over 12 months, in about 50 families. The responsiveness of the families to different dietary compositions and effects on body weight control and obesity related risk factors will be assessed during the dietary intervention study, with specific focus on changes in body weight and composition, appetite measures, adipose tissue gene expression and risk factors for cardiovascular disease (CVD) and type-2 diabetes. The role of genetic, environmental, social and cultural factors as well as their interactions with the studied diets on body weight control or development of obesity will also be investigated.

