### Diets and randomization

Families will be randomised into 5 dietary groups during dietary intervention periods 1 and 2:

Group 1: Normal protein/low GI  
Group 3: High protein/low GI  
Group 5: Control diet

Group 2: Normal protein/high GI  
Group 4: High protein/high GI

The eligible families will be stratified based on centre, number of obese parents and BMI. Within the strata the subjects will be randomized to treatment (and sub-study groups) using a simple block randomization method by a third party having no knowledge of the subjects that may affect the outcome of the study.

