## 4.2 METHOD OF ASSIGNING FAMILIES TO DIETARY GROUPS

The eligible families will be allocated to a dietary intervention group using a simple block randomization procedure with centre, number of obese parents in the family and BMI (greater or less than 34, screening value) as stratification criteria by a third party with no knowledge of the

subjects that may affect the outcome of the study. Approx. 11 families are randomized to each of the 5 dietary intervention groups. The outcome in the dietary intervention groups will be compared to each other and to the control group.

Approx. 6 subjects in each dietary group (3 men and 3 women) will be randomized to **Subgroup a** (7-day food record, BMR and DLW measurements, physical activity using pedometers, meal test). Approx. 7-10 subjects in each dietary group will be randomized to **Subgroup b** (extra fat biopsy day 3 into LCD diet).

Participation by (adult) subjects in the sub-groups is entirely voluntary and separate information sheets and consent forms will be signed.

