### **8.2.6 STATISTICAL METHODS FOR SECONDARY OBJECTIVES**

ANCOVA will be used to compare the secondary variables at week 26 between treatment groups using the relevant data from CID2 (after weight-loss, adults) or CID1 (children) as covariate.

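### The ANACOVA adjusts for the baseline value but not for the factors that stratify the randomisation, a modest and conservative loss of precision

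*Protocol*

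**What the plan says.** Section 4.2 allocates families in blocks "with centre, number of obese parents in the family and BMI (greater or less than 34, screening value) as stratification criteria". The synopsis (Diets and randomization) names the same three factors: "The eligible families will be stratified based on centre, number of obese parents and BMI".

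The analysis sections name one covariate. For the main outcomes at weeks 26 and 52, Section 8.2.4 compares groups "using the data from CID2 (after weight-loss, adults) or CID1 (children) as covariate". Section 8.2.5 conditions both the null and the alternative hypothesis on that same value. Section 8.2.6 compares secondary variables at week 26 "using the relevant data from CID2 (after weight-loss, adults) or CID1 (children) as covariate". The sample-size text in Section 8.2.7 also speaks only of controlling for the baseline value. Section 8.2.5 sends categorical variables to Fisher's exact test and time to withdrawal to the log-rank test, with no stratification named.

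On the unit and the scale: "Families will be randomised into 5 dietary groups during dietary intervention periods 1 and 2". The synopsis (Aims) describes "350 families in 8 European countries", while Section 3 describes about 50 families in Denmark, and Section 4.2 adds "Approx. 11 families are randomized to each of the 5 dietary intervention groups".

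**The concern.** Stratified blocking makes the arms more alike on the chosen factors than simple randomisation would. The true variance of a between-arm difference then no longer contains the between-stratum part. A model without the strata still estimates a residual variance that does contain it. Its standard error is therefore larger than the design warrants, and the gain that stratification was meant to bring is not collected.

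What is at stake is precision, in a trial planned to detect 1 kg. The background section itself criticises earlier glycaemic-index studies for lack of statistical power. The factors are already recorded for allocation, so the loss is avoidable.

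**Working it through.** **Inputs from the protocol (Sections 8.2.5 and 8.2.7).** Difference 1.0 kg, SD 2.5 kg, power 80%, two-sided 5%, unpaired t-test, 125 per group.

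**The plan's own figure.** n = 2(1.960 + 0.842)² × 2.5² / 1.0² = 98.1, so 99 per group (100 with the t distribution), against the stated 125. An unstated 20% drop-out would give 100/0.8 = 125. That is a separate matter. Below, 125 is used only as the stated group size.

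**Assumed input.** R² is the share of residual variance, after the baseline value, that the strata explain. The protocol does not give it, so a range of 0 to 15% is shown. Zero belongs in the range: in a single-centre analysis centre is constant, and CID2 weight probably absorbs part of the BMI stratum.

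**Formulas.**
- Excess width of the confidence interval = 1/√(1 − R²) − 1.
- Participants lost, as part of 125 = R² × 125.
- True two-sided size of the baseline-only test = 2[1 − Φ(1.96/√(1 − R²))].
- Nominal standard error = 2.5√(2/125) = 0.316 kg; true standard error = 0.316√(1 − R²).
- Power without strata = Φ[(1 − 1.96 × 0.316)/true SE]; with strata = Φ[1/true SE − 1.96].

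| R² | CI wider by | Lost of 125 | True size | Power without strata | Power with strata |
|---|---|---|---|---|---|
| 0 | 0% | 0 | 0.0500 | 0.885 | 0.885 |
| 0.05 | 3% | 6 | 0.0443 | 0.891 | 0.901 |
| 0.10 | 5% | 12.5 | 0.0388 | 0.897 | 0.915 |
| 0.15 | 8% | 19 | 0.0335 | 0.904 | 0.929 |

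The gain from adding the strata is thus about 1, 2 and 2.5 power points at R² of 5, 10 and 15%.

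**Simulation.** Five arms, 32 strata (8 centres × 2 × 2), blocks within strata, 320 families of two adults, 2,000 runs per setting. With no correlation within families, the baseline-only test had size 0.040 at R² = 0.05 and 0.036 at R² = 0.10. With strata in the model it was 0.047 in both. The Monte Carlo standard error is about √(0.05 × 0.95/2000) = 0.005, so these agree with the formula.

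**Family as the randomised unit.** With two adults per family, the design effect is 1 + ICC. For an assumed ICC of 0.05 to 0.3 it is 1.05 to 1.3, and an analysis that treats adults as independent has size 2[1 − Φ(1.96/√(design effect))] = 0.056 to 0.086. This runs the other way from the strata effect. In the simulation with ICC 0.2 and R² = 0.10, size was 0.055 without strata and 0.071 with strata but no family term. Across R² of 0 to 0.20, adding the strata alone left size at about 0.07 to 0.08.

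**The case against.** Four points can be made against this.

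First, covariates beyond baseline are commonly listed in a statistical analysis plan, and Section 8.2.4 does not say that the baseline value is the only one. This carries some weight. But the protocol names the covariate in Sections 8.2.4, 8.2.5 and 8.2.6, always the same one, and an analysis that follows that text omits the strata.

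Second, the loss may be negligible. This stands as a limit on size: R² is assumed, and centre matters only where centres are pooled. The 125 per group (5 × 125 = 625) far exceeds the approximately 110 adults to be randomised according to the synopsis, so the stated power implies pooling. A Danish analysis on its own would gain nothing from centre.

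Third, a reader might infer that the planned standard errors are simply too large. The documents do not support that. It is true of the strata taken alone, but families are randomised and individuals are compared, which makes standard errors too small. The net direction depends on an R² and an ICC that the documents do not give.

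Fourth, a reader might extend the argument to Fisher's exact test and the log-rank test and want both replaced. The variance formula is for linear models. In logistic regression, adjustment moves the odds ratio from a marginal to a conditional one and does not shrink its standard error. With about 11 families per arm locally, logistic GEE with several stratum terms would risk sparse cells. Fisher's exact test is a defensible choice there.

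**Conclusion.** The mismatch is real: the protocol specifies a model without the factors it randomises by. It is a point of precision, not of validity. Taken alone it does not bias the diet effect or inflate type I error. Under an assumed R² of 0 to 15% beyond baseline, it widens confidence intervals by 0 to about 8% and wastes the equivalent of 0 to 19 of 125 participants per group. The lower end is plausible for a single-centre analysis of weight; the upper end requires pooled centres that differ materially. The correction is worth making because it uses data already held, but only together with a term for family.

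**What to change.** In Sections 8.2.4 and 8.2.6, state that the ANACOVA includes, besides the CID2 value (adults) or CID1 value (children):

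- number of obese parents and BMI stratum, coded as used at randomisation, as fixed effects;
- centre as a fixed effect wherever centres are pooled;
- a random family effect, or standard errors clustered on family.

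The conditioning in Section 8.2.5 should be brought into line. Stratifying the log-rank test for withdrawal by centre in the pooled analysis is optional. Fisher's exact test can stay as it is for this point.

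The cost is a sentence in each section and a few degrees of freedom. No new data are needed, since the stratification factors and family membership are already recorded for allocation. The family term may widen intervals where relatives' outcomes are correlated; that corrects an overstatement of precision and is not a cost of adding the strata.

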### 5.1 INCLUSION CRITERIA

The inclusion criteria for the families are as follows:

- Families where both parents are < 65 years old, and where minimum one adult parent is obese (BMI>30) and the other parent is BMI>28.
- Families with 1-3 children, where at least one child aged between 5 and 18 years is overweight (defined according to Cole *et al.* (2), i.e. with an iso-BMI>25).
- Single-parent families with one obese (BMI>30) parent and minimum 1 overweight child aged between 5 and 18 years. Any other adult family members (including offspring) are excluded from the study. Children above the age of 16 may be excluded if they so wish.
- Healthy and no regular medication (exception oral contraceptives)
- All ethnic groups are allowed inclusion
- Smoking is allowed, provided subjects do not intend to change their smoking behaviour.
- All subjects should have an overall physical and psychological condition that the investigator believes is in accordance with the overall aim of the study.

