### **7.1.2. VISITS FOR CHILDREN (NB: No questionnaires are completed by children)**

#### **7.1.2.1 Visit 1, Screening (between week -12 and -9) (all children)**

Subjects/families will be allocated a screening number before the screening registrations are carried out. The screening registrations will include:

- Medical history including demographic data and physical examination
- Anthropometric measures: height, weight, etc

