### **7.3.3 BLOOD COAGULATION FACTORS, HORMONES, PEPTIDES & OTHERS**

In adults, fasting blood samples for the analysis of coagulation factor VIIc, fibrinogen, C-reactive protein, adiponectin, ghrelin and other relevant peptides, hormones or markers of appetite regulation, body metabolism, inflammatory responses, or obesity related diseases will be taken on CID 1-4. Blood for analysis of various adipokines/cytokines and peptides will be taken on CID 1-3 (adults only), and blood for DNA extraction will be taken on CID 1.

In children, fasting blood samples for the analysis of glucose, insulin, Insulin-like Growth Factor-1 (IGF-1), IGF Binding Protein-3 (IGFBP-3) or other relevant markers for growth, appetite regulation, glucose homeostasis, cardiovascular risk etc. will be taken.

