### 8.2.2 MAIN OUTCOME MEASURES

The main outcome measures in this study for adults are body weight loss maintained (kg), changes in body composition (DEXA/bioimpedance), proportion of subjects maintaining > 0, 5 and 10% of initial weight loss, and drop-out rate. Main outcome measures for children are changes in the proportion of overweight and obese children at 6 and 12 mo, and changes in age-associated BMI, % whole body fat and drop-out rate.

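### The children's ANCOVA adjusts only for the CID 1 value; adding sex and age would sharpen the comparison for continuous outcomes that are not already age- and sex-standardised

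*Protocol*

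**What the plan says.** Protocol 8.2.4 compares the main outcomes at weeks 26 and 52 by analysis of covariance "using the data from CID2 (after weight-loss, adults) or CID1 (children) as covariate". The hypotheses in 8.2.5 condition on the same single value. Section 8.2.6 repeats the model for secondary variables at week 26, "using the relevant data from CID2 (after weight-loss, adults) or CID1 (children) as covariate".

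Under 5.1, each family must be one in which "at least one child aged between 5 and 18 years is overweight". The main outcomes for children in 8.2.2 are the proportion overweight or obese and "changes in age-associated BMI, % whole body fat and drop-out rate"; the synopsis (Aims) has only "changes in BMI, and % whole body fat". Secondary outcomes for overweight children (8.2.3) include waist-hip ratio and blood parameters. Section 7.3.3 lists among the children's blood analyses "Insulin-like Growth Factor-1 (IGF-1), IGF Binding Protein-3 (IGFBP-3) or other relevant markers for growth".

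Age and gender enter the analysis text only in 8.2.3, as possible moderators of response tested by interaction. The screening visit for children (7.1.2.1) records "Medical history including demographic data and physical examination". The stratification factors in 4.2 are centre, number of obese parents and BMI.

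**The concern.** A child's CID 1 value carries differences in level. It does not fully carry differences in expected change. Two children with the same CID 1 value of body fat or IGF-1, one young and one adolescent, or one boy and one girl, may be expected to move differently over the following months. If the model has no term for age or sex, that predictable change is counted as noise in the diet comparison.

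No children's outcome has a sample-size calculation (8.2.7), and the number of children follows from how many families are recruited. Adjusting for characteristics already recorded is one of the few ways to gain precision without enrolling more families. The moderator analysis in 8.2.3 does not do this, because it asks whether the diet effect differs by age or sex and does not adjust the main comparison.

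**Working it through.** **The plan's own figure.** There is none for children. The only sample size, 125 per group in 8.2.7, is for adult weight change. With its stated inputs (1.0 kg, SD 2.5 kg, two-sided 5%, 80% power) the t-test needs 100 per group. The figure 125 equals 100/(1 - 0.20), but 8.2.7 states no 20% drop-out allowance. That is a separate matter and has no bearing here.

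**Time from covariate to outcome.** CID 1 for children falls between week -12 and week -9 (7.1.2.2).
- Week 26: 26 + 9 = 35 to 26 + 12 = 38 weeks.
- Week 52: 52 + 9 = 61 to 52 + 12 = 64 weeks. This applies to the main outcomes only, since 8.2.6 covers week 26.

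**Which outcomes the point reaches.**

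| Children's outcome | Method in the protocol | Does the point apply? |
|---|---|---|
| Proportion overweight/obese | Fisher's exact test (8.2.5) | No |
| Drop-out | Fisher's exact or log-rank test (8.2.5) | No |
| BMI | ANCOVA | Not if standardised for age and sex |
| % whole body fat | ANCOVA | Yes |
| Waist-hip ratio, blood parameters (IGF-1, IGFBP-3 and others) | ANCOVA (8.2.6) | Yes |
| Kidney and bone markers (7.6.3) | No ANCOVA stated | Not covered |

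**Size of the gain.** Let r² be the share of the variance left after the CID 1 value that age and sex explain. The residual variance becomes (1 - r²) times its former value, and the equivalent gain in sample size is 1/(1 - r²) - 1. The documents give no r², so it is varied as an assumption.

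For power, take five arms of n children (N = 5n), treated as independent, and an effect that gives 80% power with the CID 1 value alone. Adding two terms multiplies the standard error by √(1 - r²) × √[(N - 7)/(N - 9)] and lowers the degrees of freedom from N - 6 to N - 8. Power then follows from the noncentral t distribution. The value n = 11 corresponds to one child in each of the roughly 11 families per arm (4.2). The value n = 125 is borrowed from 8.2.7 as a large-group reference and is not a count of children.

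| r² (assumed) | Equivalent extra children | SE ratio, n = 11 | Power, n = 11 | SE ratio, n = 125 | Power, n = 125 |
|---|---|---|---|---|---|
| 0 | 0% | 1.022 | 78.3% | 1.002 | 79.9% |
| 0.05 | 5% | 0.996 | 80.3% | 0.976 | 81.9% |
| 0.10 | 11% | 0.969 | 82.4% | 0.950 | 83.9% |
| 0.20 | 25% | 0.914 | 86.5% | 0.896 | 87.8% |
| 0.30 | 43% | 0.855 | 90.6% | 0.838 | 91.7% |

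At n = 11, r² = 0.02 gives 79.1%, so the two terms pay for themselves somewhere between 2% and 5%.

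**Is that range of r² plausible?** An illustrative simulation used ages uniform from 5 to 18, a within-child correlation between visits of 0.7 to 0.95, and a baseline level rising by 0, 0.5 or 1 SD per SD of age. The r² was 0 to 0.08 when age and sex had no effect on change, 0.02 to 0.14 with effects of 0.1 SD, and 0.09 to 0.34 with effects of 0.2 SD. These inputs are also assumptions. They show that the gain can be anything from nil to substantial.

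**The case against.** The strongest reply is that nothing here is an error. ANCOVA on the baseline value is valid in a randomised trial, 8.2.4 does not forbid further covariates, and an analysis plan that is not shown could add them. This stands as far as validity goes. The point remains because the protocol names the same single covariate in 8.2.4, 8.2.5 and 8.2.6, and covariates added once the data are known carry less weight.

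Second, the 5-18 range may not describe body fat. The visit lists (7.1.2.2, 7.1.2.5, 7.1.2.9, 7.1.2.11) limit body composition to overweight children older than 12, whereas sections 3 and 7.2.3 set no age limit for overweight children. Under the visit lists, and assuming uniform ages, the SD of age falls from 13/√12 = 3.75 to 6/√12 = 1.73 years. The gain for body fat would then probably be smaller and the groups smaller too.

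Third, the CID 1 value already carries much of the difference due to age and sex. That is correct, and it is why r² is defined as what remains after it.

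A reader might infer more than the documents support:
- *That the comparison is biased by chance age imbalance.* Under randomisation it is not. Such imbalance is already reflected in the standard error and is the same precision point seen from another side.
- *That every children's outcome is affected, including bone markers.* The table of outcomes shows otherwise.
- *That the adult models need the same change.* Nothing in the protocol or in the figures above shows this.

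**Conclusion.** The point holds as a matter of efficiency. For % whole body fat, waist-hip ratio and blood parameters such as IGF-1 and IGFBP-3, the protocol's model leaves age- and sex-related change in the error term over 35-38 weeks, and for body fat also over 61-64 weeks. The randomised comparison stays valid.

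The gain is worth about 5% to 43% more children if age and sex explain 5% to 30% of the variance left after the CID 1 value. Those percentages are assumptions, and no documented figure narrows them. The power figures also treat the children as independent, although families are the unit randomised. If age and sex explain nothing, the loss is about 2 power points at 11 per group and 0.1 point at 125 per group. The possible gain outweighs that loss, so the change is worth making, but it is an improvement in precision and not the repair of a fault.

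**What to change.** In 8.2.4 and 8.2.6, state that children's continuous outcomes not already standardised for age and sex are analysed with the CID 1 value plus sex and age at CID 1. Enter age as a linear term. Allow a richer form, such as a curve or an age-by-sex term, only if numbers permit and only if it is specified in advance. At about 11 families per arm the linear form is safer, although it will not capture a marker that rises and then falls through puberty.

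Say in 8.2.2 whether the age-associated BMI is standardised for sex as well as age, and align the synopsis. If it is standardised for both, it needs no extra terms; if BMI is analysed unstandardised, it belongs with the other outcomes. Leave the tests for the proportion overweight or obese and for drop-out as they are.

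The cost is one sentence in each of the two sections and two degrees of freedom. Demographic data are already taken at screening, so no new measurement is needed.
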